## Abstract

**Background:**

Child criminal exploitation is a form of child abuse that poses a serious risk to the welfare, safety, and wellbeing of young people. Multisystemic therapy (MST) is an intensive family and community-based intervention for young people with anti-social behavioral problems, many of whom will be at risk of criminal exploitation. This protocol describes a pilot feasibility study and process evaluation, designed to examine MST for children at risk of criminal exploitation.

**Methods:**

This pilot feasibility study and process evaluation involves two phases with associated subphases: phase 1.1 involved the collaborative refinement of the logic model adapting MST for children at risk of criminal exploitation; phase 1.2 involved pre-pilot interviews with MST therapists, families, and young people; phase 2.1 is a pilot modeling study of MST for children at risk of criminal exploitation, and; Phase 2.2 is a process evaluation that will involve interviewing stakeholders, MST therapists and employees, families, and young people. The dataset for the process evaluation will include questionnaires completed by parents and young people at baseline, mid-treatment, end of treatment, and 6 months after treatment. We will supplement these data with participant-level data linkage from MST sites and services.

**Results:**

Accrual to the pilot stage of this project opened on 6th August 2021 and is due to close on 31st May 2022. We aim to publish the results of this feasibility study and process evaluation in 2023.

**Conclusions:**

The results of this feasibility study and process evaluation will inform the decision as to whether it is advisable to progress to a pilot clinical trial of MST for children at risk of criminal exploitation.

**Trial registration:**

Trial registration: ISRCTN registry, ISRCTN16164816 on 25th January 2021—https://doi.org/10.1186/ISRCTN16164816.

## Background

Child criminal exploitation (CCE) is where ‘an individual or group takes advantage of an imbalance of power to coerce, control, manipulate, or deceive a child or young person under the age of 18 into any criminal activity in exchange for something the victim needs or wants, for the financial or other advantage of the perpetrator or facilitator, or through violence or the threat of violence’ [1]. CCE is a form of child abuse and, in some circumstances, can meet the definition of modern-day slavery and is commonly seen in youth gangs [2]. Safeguarding children and young people at risk of CCE, or gang involvement, is fundamental to protect the welfare, well-being, and safety of children and young people, families, and communities. There are few well-developed interventions to support this specific group of vulnerable children and young people. There are also significant challenges in engaging this group in interventions and research such as difficulties identifying children at risk of CCE; children not seeing themselves as being a victim of abuse; families being at crisis point and having little time to engage with services and research; families and young people distrusting new individuals entering the family system (i.e., practitioners, researchers) and fear of gangs/those who have exploited the young people seeking retribution. Developing and testing appropriate interventions and engagement methods for this group and their families, while finding effective and appropriate ways to engage this group in research, is critically important.

Multisystemic therapy (MST) is an intensive family-based intervention designed to support young people with antisocial behaviors. There is evidence that MST leads to a small but significant reduction in criminal offending behavior among children and adolescents [3]. Van der Stouwe et al. [3], in their meta-analysis of MST, reported that this effect was only present when participants were offenders and younger than 15 years; larger effect sizes were associated with the successful completion of treatment, and longer duration treatment. Further, effect sizes increased when the comparison group received a single and non-multimodel intervention as treatment-as-usual (TAU). Treatment effects were moderated by study characteristics, such as the study taking place in the USA, efficacy designs, and studies rated as higher quality. The effect on delinquency was moderated by changes in externalizing behavior, substance abuse, parenting skills and mental health, and placements away from home. Treatment for those with a history of sexual offending behavior was also associated with larger effect sizes.

It is of particular note that studies examining MST tend to report smaller effect sizes when located outside of the USA, for example, within Scandinavia [4–6] or Canada [7]. A recent Campbell Collaboration systematic review and meta-analysis [8] included 23 MST trials published between 1983 and 2020. They highlighted the inconsistency of study outcomes and findings, the mixed quality of the studies, and the high risk of bias in these studies. Overall, they found that, outside the USA, there is a lack of evidence that MST is effective.

In the United Kingdom, Butler et al. [9] completed a small randomized controlled trial of MST, reporting that the intervention led to improvements in recidivism over and above TAU within Youth Offending Teams in North London. This group went on to complete a large single-blind randomized controlled trial comparing MST to TAU within England [10], reporting that MST did not lead to a significant reduction in out-of-home placements, nor did it reduce the time to the next offense episode. The average number of offenses committed by participants at the 18-month follow-up was significantly greater for those who had received MST. Those who scored low on callous and unemotional traits had poorer outcomes at follow-up. The authors suggested that these outcomes may be associated with the relatively well-resourced nature of services for young offenders within the United Kingdom, including increased flexibility to respond to the treatment needs of young offenders, in comparison to the USA. A 5-year follow-up of the same families also found no difference between MST and TAU for offending behavior [11, 12]. However, a qualitative study interviewing these same young people 4 years after the completion of this trial found that the male participants who took part in MST had more mature profiles as they transitioned into adulthood than those who took part in TAU [13].

In order to deal with some of these challenges, a series of proposed augmentations to the standard MST protocol for children and teenagers who are at risk of criminal exploitation were proposed, which may increase the effectiveness, especially for those at risk of criminal exploitation. The proposed changes included:Extending the length of treatment to 4–6 months, which has been previously associated with larger effect sizes [3],The inclusion of psychoeducation about criminal exploitation,Expansion of the content of therapy to include a greater focus upon teaching coping skills, safety planning, trauma-focused work, substance misuse work, and addressing both distorted cognitions and social skills,Ensuring that the expectations and the content of any intervention are developmentally appropriate for children who are aged 10 to 12,The inclusion of setting clear expectations about curfews and peers,Targeting factors that lead to greater inclusion within the home environment, and reduce conflict between young people and adults,Increased supervision and monitoring of social media,Increased plans to retrieve a younger person if they go missing in collaboration with agencies (e.g., police),Increased safety planning around risky behaviors at home and in the community (e.g., weapons, aggression),Increased focus on de-escalation techniques to reduce family conflict,Increased focus on increasing pro-social peers and activities,Inclusion of training and resources for working with young people who are involved with risky adults/gangs, inclusive of mapping contacts with negative peer groups,Increased focus on the promotion of relationships with positive adults within the community,An increased focus on communication with parents,Working with primary schools, especially around periods of transition to secondary schools,Increased work to reduce exclusions and weapon carrying, andIncreasing the focus on working collaboratively with agencies.

Taking the aforementioned literature and proposed augmentations to MST into account, the aim of the current project is to examine the feasibility of MST for children at risk of criminal exploitation, an augmented version of MST, adapted specifically for children and young people aged 10 to 15 years of age who are at risk of criminal exploitation. To achieve this, we will complete a modeling study within existing services to test the proposed changes to the standard MST protocol using process evaluation, and qualitative and quantitative research methods. The primary purpose of this methodology is to collect data to allow for the estimation of parameters necessary to inform the decision to proceed with a pilot clinical trial.

### Research questions

Our research questions are as follows:

Primary research question: (a) Is it feasible to complete a pilot trial of MST for children at risk of criminal exploitation within existing services within England?

Secondary research questions: (b) Do families, children and young people, clinicians, and other stakeholders consider MST for children at risk of criminal exploitation an acceptable intervention, and (b) what are the likely factors that will facilitate or hinder the successful implementation of MST for children at risk of criminal exploitation and how can they be successfully managed?

## Methods

### Study objectives

The objectives of this study are to:Collaboratively refine the logic model which represents the causal processes through which MST for children at risk of criminal exploitation leads to a reduction in criminal offending behavior. This logic model will be used to directly inform our process evaluation which will consider, but is not limited to (i) the impact of additional staff training, (ii) how partnerships with stakeholders are strengthened, (iii) the processes that promote or hinder greater engagement with voluntary and community agencies and other positive activities, and (iv) the processes that increase or hinder engagement in education and school transition.To undertake interviews with clinicians, stakeholders, families, and young people to refine MST tools for working with families where there is a risk of criminal exploitation, including adaptations to any existing fidelity checklists, and to consider the most appropriate method of measuring outcomes from MST for children at risk of criminal exploitation.To complete a single-group modeling study of MST, for children at risk of criminal exploitation, with 50 families receiving treatment within existing MST services, in order to estimate: (i) the acceptability and feasibility of MST for children at risk of criminal exploitation for stakeholders, including families, (ii) patient and clinician satisfaction with the intervention, (iii) the appropriateness of our measures in terms of their use within a future pilot trial, (iv) the appropriateness of an adapted fidelity checklist (if possible), (v) the accrual rate and willingness of teams to recruit participants, (vi) therapy completion rate and attrition, and (vii) the within-group effect size.

In addition, we will sample families, stakeholders, and clinicians to complete in-depth interviews as part of our process evaluation to further consider whether the augmentations to the current MST protocol for children at risk of criminal exploitation were successfully implemented, with reference to our logic model, and any associated factors that facilitated or hindered the successful implementation.

### Design

This is a pilot feasibility study and a process evaluation of MST adapted for children at risk of criminal exploitation. The project is composed of two phases with subphases and takes place over 24 months:

#### Phase 1

There were two complimentary workstreams within this Phase. Phase 1.1: We hosted three initial collaborative meetings between researchers and MST experts to finalize the logic model to be used in order to formalize the indicators that we will measure within our process evaluation. As discussed within our objectives, these will include, but are not limited to, (i) the impact of additional staff training, (ii) how partnerships with stakeholders are strengthened, (iii) the processes that promote or hinder greater engagement with voluntary and community agencies and other positive activities, and (iv) the processes that increase or hinder engagement in education and school transition. The purpose of these meetings, in addition to finalizing the logic model, was to consider the most valid method of measurement associated with each of our key indicators. Phase 1.2: We completed group and one-to-one interviews with clinicians, stakeholders, families, and young people with participants from across our four sites in England: (a) Birmingham (b) Nottingham (c) Yorkshire, and (d) Sandwell. The aims of this stage were to refine MST tools for working with families at risk of criminal exploitation, including adaptations to existing fidelity checklists, and to consider the most appropriate method of measuring outcomes from MST for children at risk of criminal exploitation. Within each group, the proposed changes to standard MST were discussed, along with selected outcome measures, and the MST Therapist Adherence Measure–Revised (TAM-R). Participants were asked to consider each proposed change, outcome measure, and the fidelity checklist in turn, and were encouraged to consider the likely benefits, disadvantages, and any associated implementation challenges. Each interview was recorded and transcribed. Transcriptions were analyzed using Framework Analysis [14]. The findings were considered by the study and delivery team collaboratively, responding to recommendations by making necessary changes as appropriate.

#### Phase 2

Within Phase 2, we are currently accruing participants for a single-group modeling study of MST for children at risk of criminal exploitation with 50 families within existing MST services to estimate the parameters necessary to inform the decision as to whether a pilot trial should be completed. We will examine (i) the acceptability and feasibility of MST for children at risk of criminal exploitation for stakeholders, including families, (ii) patient and clinician satisfaction with the intervention, (iii) the appropriateness of our measures in terms of their use within a future pilot trial, (iv) the appropriateness of an adapted fidelity checklist, (v) the accrual rate and willingness of teams to recruit participants, (vi) therapy completion rate and attrition, and (vii) the within-group effect size. We will also complete in-depth interviews with 12 families (6 who have successfully completed treatment, and 6 who have discontinued treatment but have consented to be interviewed) and 12 clinicians and stakeholders as part of the process evaluation, and to further investigate acceptability.

#### Phase 3

We will request anonymized data for all MST participants from the MST-I database. This database is located in the USA and contains data about all families who complete MST. These data will include demographic information (e.g., age, gender, ethnicity), treatment information (e.g., length of treatment, whether treatment was completed), and key outcome data (e.g., parent feedback about MST, whether the young person is in school, remained living in the family home, or has offended since taking part in MST, SDQ, if taken). Parents/carers consent to these data being added to the MST-I database and reported/analyzed anonymously as part of their MST participation agreement paperwork. Participating organizations have already collected and stored these data as part of their substantive roles. We will be paying the organization that runs the database (MST-I) an administrative fee to cover all of their costs related to producing and sending us an anonymized dataset. We will analyse and report these data.

### Randomization and blinding

As this is a feasibility study, using a single group of participants, randomization will not be tested. Testing randomization and the associated procedures would be completed within a future pilot trial which would aim to estimate the parameters necessary to inform the decision to undertake a Phase III clinical trial. However, as part of in-depth interviews with families and clinicians, willingness to be randomized to MST for children at risk of criminal exploitation + Treatment as Usual (TAU) vs. TAU will be investigated.

Considering that this is a feasibility study, masked assessors will not be used. However, again, as part of our in-depth interviews, how participants understand, and whether they accept masking, and the use of associated procedures to maintain masking, will be investigated with participants and clinicians.

### Study setting

This study is taking place within community-based settings in England. Sites are based in Birmingham, Sandwell, Yorkshire, and Nottingham, within existing MST services. Study sites have adopted a multi-agency approach to recruitment and invite referrals from social services, youth offending teams, child and adolescent mental health services, and education. The steps in the pathway for the pilot are as follows: families are informed about the screening process and if they do not opt-out, they are screened for eligibility to take part in MST for children at risk of criminal exploitation. Participants who meet these criteria are assigned to receive MST for children at risk of criminal exploitation and complete an initial baseline assessment within 4 weeks before starting MST treatment. MST for children at risk of criminal exploitation will last for up to 6 months, and an additional assessment period will occur at the mid-point of treatment (at 3 months, although sometimes shorter depending on the length of treatment), the end of treatment (approximately 6 months), and at 6-month follow-up. Young people, families, therapists, and key stakeholders will also be invited to take part in an interview as part of the process evaluation and our investigation of the acceptability and experience of treatment. Further information can be found in the participant flow diagram (Fig. 1).

**Fig. 1 Fig1:**
[figure not shown]
RESET Study flow diagram

### Fidelity and adherence

In collaboration with the delivery team and MST-UK, we will consider making appropriate augmentations to the existing MST instrument, the TAM-R [15–17] which is used routinely within MST as a measure of therapist fidelity. We will also record and report the number of sessions received, as well as the attrition rate.

### Inclusion criteria and exclusion criteria

We are currently in the process of recruiting 50 children and young people aged 10 to 15 years who have a history of engaging in antisocial behavior. Our eligibility criteria have been adapted from a successfully completed phase III trial of MST [10].

### Inclusion criteria

The inclusion criteria for pilot participants are as follows:Children aged between 10 and 15 yearsParental consent to take partThe child is at risk of exploitation, as evidenced by:(A)Either the child or family having disclosed information to indicate that the child is at risk of another individual or group taking advantage of an imbalance of power to coerce, control, manipulate, or deceive them into any criminal activity in exchange for something the victim needs or wants, for the financial or other advantage of the perpetrator or facilitator or through violence or the threat of violence;(B)Or there is evidence of at least two of the following present which suggests that a child is at risk of exploitation:i.A criminal conviction, or a final warning, cautions, or reprimands within the last year,ii.Exhibiting weekly aggressive behavior which is of a significant risk to others (e.g., sexually abusive behavior, physical fighting) outside the home,iii.At least one period of having gone missing, even for a few hours, within the last 6 months,iv.History of substance misuse (alcohol or drugs),v.History of permanent school exclusion,vi.Association with peers or adults who are seen by others to have had a negative influence upon the child.

### Exclusion criteria

Our exclusion criteria for pilot participants are as follows:

The family refuses to take part in the study.The young person lives independently, or a primary caregiver cannot be identified.The child is presenting with symptoms consistent with a psychotic illness.The child is at high risk of suicide as assessed by the clinical team assessing the referral.There is documented evidence of the child having a Full-Scale IQ < 65.There is evidence to indicate that a family member who is living with the child has been sexually abusing them and there continues to be an active and enduring risk,The child has previously received a diagnosis of an autism spectrum disorder and problematic behaviors as defined within the inclusion criteria have been judged to be associated with having a developmental disability (e.g., self-harm associated with hypersensitivity) by the clinical team assessing the referral.

### Sampling

For phase 1 of this study, we worked collaboratively with the delivery team and their partner organizations to identify and invite potential participants to take part in our interviews. Phase 2: In order to maximize the probability of successful recruitment, we have adopted a multi-agency approach to recruitment and invite referrals from social services, youth offending teams, child and adolescent mental health services, and education. Fifty children and teenagers from one of three geographical regions in England (i.e., Birmingham and Sandwell, Nottingham, Yorkshire) who have met the eligibility criteria for the study, along with their families, will be invited to take part. As this is a feasibility study, and the purpose is to provide estimates of key parameters for a future pilot trial rather than to power the current study to detect statistically significant differences, a formal a priori power calculation has not been conducted [18]. However, recruiting 50 participants will provide a certain level of precision around a 95% confidence interval regarding the estimate of within-group effect. For example, the 95% confidence interval associated with a sample size of 50 is ± 13.8. We therefore believe that this sample size will provide reasonable precision around our estimates of parameters which will be used to inform the design and decision to proceed to a pilot trial including an estimate of the standard deviation of the outcome measures. We will also recruit 48 participants to take part in our interviews about the interventions which will contribute to the decision as to whether to proceed to a definitive trial. However, should a decision be made to proceed to a trial within a future study, it would be appropriate to recruit a larger sample than what we have proposed for inclusion within this feasibility study in order to model the parameters (e.g., randomization) necessary to inform the decision to proceed to a phase III trial.

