### Progression criteria

Green: (a) intervention acceptability: all stakeholders, including families judge the intervention and the associated changes from standard MST to be acceptable, (b) candidate outcome measures: 95% of recruited participants complete the outcome measures on all occasions and rates of missing data are below 5%, (c) fidelity checklist: an adapted fidelity checklist is judged to be acceptable by stakeholders with a completion rate of 95%, and (d) recruitment and retention: 100% of participants are recruited, the accrual rate is 2:1, and the retention rate is at least 80%.

Amber: (a) intervention acceptability: some stakeholders, including families raise concerns about the acceptability of the intervention, which may include confusion about how the intervention is sufficiently different from standard MST, (b) candidate outcome measures: fewer than 95% but more than 80% of recruited participants complete the outcome measures on all occasions and rates of missing data are more than 5% but less than 10%, (c) fidelity checklist: an adapted fidelity checklist is judged to be acceptable by stakeholders with a completion rate of less than 95% but more than 80%, and (d) recruitment and retention: fewer than 100% but more than 80% of participants are recruited, the accrual rate is greater than 2:1 but less than 2.5, and the retention rate is less than 80% but higher than 70%.

Red: (a) intervention acceptability: a majority of stakeholders, including families raise concerns about the acceptability of the intervention, including confusion about how the intervention is sufficiently different from standard MST, (b) candidate outcome measures: fewer than 80% of recruited participants complete the outcome measures on all occasions and rates of missing data are more 10%, (c) fidelity checklist: an adapted fidelity checklist is judged to be acceptable by stakeholders with a completion rate of less than 80%, and (d) recruitment and retention: fewer than 80% of participants are recruited, the accrual rate is greater than 2:5, and the retention rate is less than 70%.

Where any of our criteria are judged to be amber or red, the study team will examine the likely causes and consider whether a mitigation strategy could be successfully implemented.

Where any of our criteria are judged to be amber or red, the study team will examine the likely causes and consider whether a mitigation strategy could be implemented.

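### The ± 13.8 offered as the precision of the within-group effect at n = 50 matches the half-width for a proportion, and says nothing about a mean change, a standardised effect or an SD

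*Protocol article*

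**What the plan says.** Under Sampling, the protocol article states that "a formal a priori power calculation has not been conducted", and rests the choice of 50 on precision instead. It says that the sample gives "a certain level of precision around a 95% confidence interval regarding the estimate of within-group effect". The next sentence offers an example: "the 95% confidence interval associated with a sample size of 50 is" ± 13.8. It names no unit, outcome, SD or assumed proportion. From this the section concludes that the sample provides "reasonable precision around our estimates of parameters which will be used to inform the design and decision to proceed to a pilot trial", and it counts the SD of the outcome measures among those parameters.

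Three other places bear on the point:

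- Study objectives and Analysis both list the within-group effect size among the quantities to be estimated. Analysis specifies it for the proposed primary and secondary measures.
- Data collection places the last assessment at 52 weeks from the start of treatment.
- Progression criteria set green retention at 80% or more. The amber band is where "the retention rate is less than 80% but higher than 70" per cent.

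The ± 13.8 is the only numerical precision figure in the article. Analysis promises 95% confidence intervals but gives no widths.

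**The concern.** A confidence interval half-width has the unit of the quantity estimated. A within-group effect is either a mean change on a questionnaire scale or that change divided by an SD. Neither has a half-width of 13.8 unless an SD is supplied, and the article gives none for any outcome. The figure looks like one for a percentage placed after a sentence about a different parameter.

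It is the sole numerical argument for n = 50, and the article moves from it by inference to adequate precision for the effect and the SD. A reader planning the next trial cannot tell from the text how well either will be known.

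A smaller second matter is the denominator. A within-group change needs follow-up data, so the number analysed will be below 50 if retention only just meets the plan's own green threshold.

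**Working it through.** **Inputs.** n = 50 recruited, a single group, and a 95% interval with half-width 13.8 (Study objectives; Sampling). Green retention threshold 80% (Progression criteria), hence 0.80 × 50 = 40 followed up. No SD is given anywhere, so results for changes are in SD units.

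**1. Reproducing the plan's figure.** Half-width for one proportion at p = 0.5:

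1.96 × √(0.5 × 0.5 / 50) = 0.1386, or 13.86 percentage points.

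This is 13.8 when truncated. Other intervals at p = 0.5 fit less well: t quantile 14.21, continuity-corrected 14.86, Wilson 13.36, exact about 14.5, one-sided 95% 11.63. A proportion of 0.45 or 0.55 in the same formula gives 13.79, so small departures from p = 0.5 do not alter the reading.

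**2. Could it be a mean change?** Solving 1.96 × SD/√50 = 13.8 gives SD = 13.8 × √50 / 1.96 = 49.8 raw units (48.6 with the t quantile). The article states no such SD. The candidate primary outcome is a 15-item measure with yes/no answers plus frequencies. An SD of about 50 is that of a 50/50 binary variable expressed in percent.

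**3. Precision of the parameters the text refers to.**

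- Mean within-group change, in SDs of the change score: t(0.975, n−1)/√n.
- Standardised within-group effect d (large sample): 1.96 × √(1/n + d²/(2n)). The range d = 0.2 to 0.8 is an assumption.
- SD, as a multiple of its estimate: √((n−1)/χ²) at the 97.5% and 2.5% points of χ² with n−1 degrees of freedom.

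| Parameter | n = 50 | n = 40 (80% retained) |
|---|---|---|
| Mean change, SDs of change | ±0.284 | ±0.320 |
| Standardised effect, d = 0.2 | ±0.280 | ±0.313 |
| Standardised effect, d = 0.8 | ±0.318 | ±0.356 |
| SD, multiple of estimate | 0.84 to 1.25 | 0.82 to 1.28 |

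Worked example at n = 40, d = 0.8: 1.96 × √(0.025 + 0.64/80) = 1.96 × √0.033 = 0.356.

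**4. Proportions of those recruited.** For retention or completion the denominator stays at 50. At 80% the half-width is 1.96 × √(0.8 × 0.2 / 50) = 11.1 points, so 13.86 is a conservative bound.

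**The case against.** The strongest reply is that nothing depends on the number. The quantitative analysis is descriptive, no power calculation is claimed, the progression criteria do not use ± 13.8, and it is introduced only as an example. Nor do the corrected figures show 50 to be too few: about ±0.28 SD of change, and an SD within 0.84 to 1.25 times its estimate, may well be reasonable for a feasibility study. All of that stands, and it limits the point to what the article states about its sample size. It does not rescue the statement. Precision is the justification offered in place of power, and the single figure given for it is attached to a parameter it does not describe. It is also fair to say that the article never calls 13.8 a proportion. The source is inferred, although without an SD the figure could not serve a within-group effect in any case.

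A reader might be tempted to go further in four ways that the documents do not support:

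- **That 13.8 is a miscalculation.** 13.86 printed as 13.8 is truncation and carries no weight.
- **That the whole statement ignores attrition.** For retention or completion among those recruited, 50 is the right denominator. The loss affects only quantities measured at follow-up.
- **That the plan accepts 70–80% retention.** That range is amber: the team examines causes and considers mitigation. It is a warning band, not a planning assumption.
- **That the intervals must separate the progression bands.** The criteria are thresholds for observed rates followed by the team's judgement. Nothing requires an interval to exclude a neighbouring band.

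**Conclusion.** The point holds as a mislabelled precision statement. The ± 13.8 agrees with the worst-case half-width for a proportion at n = 50 (13.86 percentage points). It therefore cannot support the precision claimed for the within-group effect or the outcome SD.

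For follow-up quantities the relevant precision at the green retention threshold is about ±0.32 SD of change for a mean change, ±0.31 to ±0.36 for a standardised effect, and 0.82 to 1.28 times the estimate for an SD. An SD at baseline, if all 50 are assessed, keeps the n = 50 limits.

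These results assume 40 of 50 followed up, a true standardised effect between 0.2 and 0.8, and approximate normality for the t and χ² limits. They do not show that 50 is inadequate, and no analysis or decision rule changes.

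**What to change.** Remove the link between ± 13.8 and the within-group effect, and replace the example under Sampling with text such as:

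> With 50 recruited, a proportion of those recruited (e.g. retention or completion) is estimated to within ±13.9 percentage points at worst (about ±11 at 80%). With 40 followed up (80% retention), a mean within-group change is estimated to within about ±0.32 SD of the change score, a standardised within-group effect to within about ±0.31 to ±0.36 (assuming a true effect of 0.2 to 0.8), and an outcome SD to within 0.82 to 1.28 times its estimate. With all 50 followed up these are ±0.28, ±0.28 to ±0.32, and 0.84 to 1.25 times.

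The claim of reasonable precision can then be kept or qualified against figures that refer to the right parameters. The cost is wording only: no extra participants and no change to the analysis, with a stated precision that becomes slightly less favourable. The article's Discussion places accrual in its final month in May 2022, so the same statement can be carried into the analysis plan and the final report.
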